#### Ultrasound-Guided Thoracic Paravertebral Injection Technique

We adopted an ultrasound-guided approach for thoracic paravertebral injection, as detailed in Pu et al. [25]. The patient will be placed in the prone position to optimize access to the thoracic paravertebral space. A low-frequency convex array ultrasound probe (2–5 MHz) will be used to localize the target thoracic levels, starting in the paraspinal sagittal position and moving caudally to identify the ribs. After identifying the first rib, the probe will be moved further down the thoracic spine to locate the target segments. Typically, one to three thoracic levels will be selected based on the dermatomal distribution of ZAP, with emphasis on the most affected segments (e.g., T3, T4, and T5 for T3–T5 involvement).

Once the target level is identified, the probe will be rotated 90 degrees to achieve an axial view, allowing visualization of the transverse process, inferior articular process (IAP), and parietal pleura (PP). A 22-gauge, 80–100-mm echogenic needle will be inserted in-plane from lateral to medial, aiming for the midpoint between the IAP and PP. Doppler ultrasound will be used to avoid puncturing vascular structures. After confirming the needle placement, 3 ml of PRP will be injected at each targeted level under continuous ultrasound guidance.

Following the injection, patients will be monitored for 30 min to observe any adverse effects. A follow-up ultrasound will be performed to verify the distribution of the injectate and exclude complications such as hematomas or pleural punctures.

#### Treatment Interval and Treatment Dose

Patients in both groups will receive standard antiviral therapy with famciclovir 500 mg 3 times daily for 7 days, initiated immediately upon recruitment during the viral outbreak [26]. In addition to the standard antiviral therapy, patients in the experimental group will receive PRP injections. The interval between each ultrasound-guided thoracic paravertebral injection is one week, with a total of four injection treatments. Each injection includes 3 ml of PRP per affected thoracic nerve.

#### Additional Intervention

Antiviral therapy has been widely used as the standard treatment for HZ [27]. During the treatment process, pain management will be adjusted based on pain severity and nature of the pain. For mild pain, non-opioid analgesics, such as NSAIDs, will be administered, with opioids added if the pain progresses to moderate or severe levels. Given the neuropathic component of ZAP, tricyclic antidepressants or anticonvulsants, such as gabapentin or pregabalin, may also be incorporated to enhance pain relief [28]. If the ultrasound-guided PRP injection is unsuccessful or the treatment cannot be completed for any other reason, the corresponding patient will be considered a protocol violation and must be excluded from the study.

After completing the study, the doctor will decide whether to continue auxiliary medications or other treatments based on the patient's specific condition. The dosage of medication will be adjusted according to changes in the patient's pain level, aiming to optimize therapeutic effects and improve quality of life. Treatments not mentioned in this protocol will not be permitted unless approved and standardized by the research team. All additional treatments will be documented in detail by the research assistant.

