### Case Dropout Instructions

If a subject develops other comorbidities, complications, or special physiological changes during the trial and is deemed unfit to continue, they will be classified as a case dropout.If a subject encounters a serious or key adverse event during the trial, and our research team judges it inappropriate to continue, the subject will be withdrawn.If a subject adds medications not specified in the protocol or receives external treatment, it will be considered a protocol violation, and they must be removed from the trial.Subjects may choose to withdraw due to personal reasons or be lost to follow-up in the final stage of the trial.

For all cases of dropout, our research team will actively complete the last follow-up and examination to collect data and analyze effectiveness and safety. Detailed information on all dropout cases, including test results and reasons for dropout, will be fully documented on the case report form.

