### Statistical Analysis

All analyses will be conducted on an intention-to-treat (ITT) and per-protocol (PP) basis to ensure the robustness of the results.

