#### Handling of Outliers and Missing Data

To address missing data, multiple imputation will be utilized. Outliers will be analyzed based on their origin and nature to determine whether correction, removal, or the application of data transformation methods is necessary to mitigate their impact.

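### Two rules take randomised patients out of the trial for events after randomisation, which contradicts the planned intention-to-treat analysis and leaves their PHN outcome unsecured

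*Protocol article*

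**What the plan says.** Three sections of the protocol article define who stays in the trial and who is analysed.

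- **Additional Intervention.** The trigger is "If the ultrasound-guided PRP injection is unsuccessful or the treatment cannot be completed for any other reason". The consequence is that "the corresponding patient will be considered a protocol violation and must be excluded from the study". This section makes no provision for collecting data afterwards.
- **Case Dropout Instructions.** If a subject adds medication outside the protocol or "receives external treatment, it will be considered a protocol violation, and they must be removed from the trial". For dropouts in general, "our research team will actively complete the last follow-up and examination to collect data and analyze effectiveness and safety".
- **Statistical Analysis.** "All analyses will be conducted on an intention-to-treat (ITT) and per-protocol (PP) basis to ensure the robustness of the results". Under Handling of Outliers and Missing Data: "To address missing data, multiple imputation will be utilized".

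The primary outcome is PHN, defined as NRS of 4 or more at months 3, 6 and 12. Table 1 places the four PRP sessions in weeks 1 to 4 and the antiviral course in week 1.

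**The concern.** An ITT analysis keeps every randomised patient in the assigned arm, whatever happens to treatment. A patient excluded from the study because an injection failed cannot also be analysed as randomised. Both rules act on events after randomisation, and neither says that it governs only the PP set.

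Follow-up matters as much as the analysis label. PRP sessions end at week 4 and PHN is first assessed at month 3. A patient excluded during treatment would therefore leave roughly two months or more before the first primary assessment. If follow-up stops there, the ITT result depends on imputing outcomes that the trial could have observed. An analysis plan written later cannot recover them.

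The injection rule is also uneven between arms. Only the PRP arm has an injection that can fail, at four weekly sessions, against a 7-day oral course for controls. The trial is open-label and the article gives no criterion for an unsuccessful injection, so the decision is made with the arm known.

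**Working it through.** **1. The plan's own figure.** Inputs from Sample Size Calculation: 34.8% PHN in controls, 10% with PRP, 5% significance, and 90% (worded as a confidence level, read here as power). The test is two-sided, from Statistical Analysis. With the pooled-variance formula and mean rate p̄ = (0.348 + 0.10)/2 = 0.224:

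n = [1.960·√(2·0.224·0.776) + 1.282·√(0.348·0.652 + 0.10·0.90)]² / 0.248² = 57.3, rounded up to 58 per group.

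This matches the stated 58. The stated 64 is 58 × 1.10 = 63.8, rounded up. The 34.8% and the 64 per arm are used below.

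**2. The injection rule, if excluded patients are left out of the analysis.** Let f be the fraction of the PRP arm excluded and q the PHN risk among those excluded. Neither is in the document. Assume no true effect, so both full arms have 34.8%. The rate among retained PRP patients is

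p = (0.348 − f·q)/(1 − f).

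Take f = 10%, so 64 × 0.90 = 57.6, or 58 PRP patients against 64 controls. The error rates come from exact binomial enumeration of the chi-square test without continuity correction.

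| q among excluded | Retained PRP rate | RR | Two-sided error | Part favouring PRP |
|---|---|---|---|---|
| 20% | 36.4% | 1.05 | 5.0% | 1.6% |
| 34.8% (average) | 34.8% | 1.00 | 4.7% | 2.5% |
| 50% | 33.1% | 0.95 | 5.3% | 3.9% |
| 60% | 32.0% | 0.92 | 6.1% | 5.1% |
| 80% | 29.8% | 0.86 | 9.0% | 8.6% |
| 100% (extreme) | 27.6% | 0.79 | 13.9% | 13.6% |

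For example, at q = 60%: (0.348 − 0.10 × 0.60)/0.90 = 0.320. With no exclusions (64 against 64) the same test has a two-sided error of 5.2%, of which 2.6% favours PRP. The bias vanishes when q is average and reverses when q is below average.

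**3. The added-treatment rule.** It applies to both arms. Take the design rates, and assume it removes 30% of patients with PHN and 5% of those without:

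- Control: 0.348 × 0.70/(0.348 × 0.70 + 0.652 × 0.95) = 28.2%, with 13.7% removed.
- PRP: 0.10 × 0.70/(0.10 × 0.70 + 0.90 × 0.95) = 7.6%, with 7.5% removed.

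The risk difference shrinks from 24.8 to 20.7 points, while RR moves from 0.287 to 0.268. With no true effect and equal removal probabilities, RR stays at 1.00. No single direction follows.

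**The case against.** The strongest reply is that the article does not abandon these patients. It promises a last follow-up for all dropouts, says their effectiveness and safety data will be analysed, and plans multiple imputation. It never states that follow-up stops, and the timing of the last follow-up is open. An ITT analysis could therefore be attempted, so it would be too strong to say that the rules defeat ITT. What remains is that nothing commits to the month 3, 6 and 12 visits. The injection-failure rule has no data clause of its own, and it is not said whether those patients count as dropouts.

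A reader might also infer that the rules favour PRP because treatment failures leave that arm. The document does not show this. An unsuccessful injection or incomplete course is, on its face, a procedural event in weeks 1 to 4, and nothing ties it to later PHN risk. The added-treatment rule covers both arms and is narrower than it looks, because NSAIDs, opioids, tricyclics and anticonvulsants are allowed and the team may approve other treatments.

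Finally, the error rates above come from leaving patients out. They put no figure on an ITT analysis with imputation. The 10% is borrowed from the general dropout allowance and applied here to one arm only. This limits how the table may be used; it does not remove the contradiction.

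**Conclusion.** The contradiction stands and should be resolved before more patients are affected. Two mandatory rules remove randomised patients for events after randomisation, without limiting the removal to the PP set, while the analysis section promises ITT. Collection of their primary outcome is not secured.

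The injection rule falls mainly on one arm and can bias the comparison. Its direction and size cannot be read from the document. With 10% of PRP patients left out and no true effect, two-sided type I error runs from 4.7% at average risk to 9.0% if 80% of them would have PHN; 13.9% is an extreme bound. That range depends on assumed values of f and q and applies only to an analysis that omits these patients. For the added-treatment rule, no direction is established.

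**What to change.** Replace the consequence in Additional Intervention ("the corresponding patient will be considered a protocol violation and must be excluded from the study") and the one in Case Dropout Instructions ("it will be considered a protocol violation, and they must be removed from the trial") with a single statement. Such patients are recorded as protocol deviations, stay in scheduled follow-up through month 12 unless they withdraw consent, are analysed in their randomised arm in the ITT analysis, and are left out only of the PP set. Multiple imputation then serves only outcomes truly not obtained. The change concerns follow-up and analysis sets, not whether treatment continues.

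The cost is a short amendment and some extra effort at visits already in Table 1. The observed ITT effect may also be smaller. If, as an assumption, 10% of PRP patients do not complete and carry the control risk, the PRP rate becomes 0.10 × 34.8% + 0.90 × 10% = 12.5%. Power with 64 analysed per group is then 0.853, against 0.929 with no such patients.

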### Follow-up and Participant Timeline

After patients receive therapy, systematic follow-up will be conducted. Follow-up time points are shown in Table 1.

**Table 1 Tab1:** Timeline of participant enrolment, allocation, interventions, and outcome assessments

Time point	Enrolment	Allocation	Post-allocation								Close out
	D0	D0	w1	w2	w3	w4	M1	M2	M3	M6	M12
Enrolment											
Eligibility screening	×										
Informed consent	×										
Allocation		×									
Intervention											
PRP treatment			×	×	×	×					
Antiviral therapy			×								
Assessment											
Demographics	×										
Incidence rate of PHN									×	×	×
NRS-11	×	×	×	×	×	×	×	×	×	×	×
Pain characteristics	×	×	×	×	×	×	×	×	×	×	×
Skin lesions	×	×	×	×	×	×	×	×	×	×	×
SF-12		×				×			×	×	×
PSQI		×				×			×	×	×
Analgesic consumption			×	×	×	×	×	×	×	×	×
Adverse events			×	×	×	×	×	×	×	×	×

*PRP* platelet-rich plasma,* PHN* postherpetic neuralgia,* NRS-11* Numeric Rating Scale (0–10) (measures pain intensity),* SF-12* 12-item Short-Form Health Survey (assesses quality of life),* PSQI* Pittsburgh Sleep Quality Index (evaluates sleep quality),* D* day,* W* week,* M* month

### Outcome Assessment

#### Baseline Demographic Characteristics

Baseline demographic characteristics of the patients will be collected through institutional electronic medical records or direct inquiry to compare with post-intervention outcomes.

#### Primary Outcome

Incidence rate of PHN: The incidence rate of PHN will be calculated based on the percentage of patients with an NRS score ≥ 4 at the follow-up visits scheduled at 3 months, 6 months, and 12 months.

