## Methods

### Study Objectives

The primary objective of this study is to assess the effectiveness of ultrasound-guided thoracic paravertebral PRP injections in alleviating acute ZAP and preventing the onset of PHN. The secondary objective is to compare the outcomes of PRP injections with traditional antiviral therapy in treating acute HZ.

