#### Primary Outcome

A chi-square test will be used to compare the incidence of PHN between the PRP treatment group and the antiviral therapy group. Additionally, the relative risk (RR) and its 95% confidence interval will be calculated to evaluate the relative risk of PRP treatment compared to antiviral therapy.

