#### Secondary Outcomes

For quantitative data (such as NRS-11, SF-12, and PSQI scores), the t-test or Mann–Whitney U test will be used to compare the differences between the two groups according to the data distribution characteristics. For categorical results (such as complication rate), chi-square test or Fisher's exact test will be used. All statistical analyses will use two-sided tests, with the significance level set to 0.05. For continuous repeated measurement data, such as quality of life scores at different time points after treatment, repeated measures ANOVA or mixed models will be used to analyze data for time effects and between-group effects.

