#### Sample Size Calculation

Based on the reported prevalence, the incidence of PHN after antiviral therapy with famciclovir after VZV relapse in patients > 50 years of age is approximately 34.8%[31]. We predict a similar incidence rate in the control group. For the PRP group, our clinical experience suggests an estimated incidence of 10%. To achieve a 90% confidence level and a 5% significance level, we used PASS V.15 software (NCSS, Kaysville, UT, USA) to estimate that a minimum of 58 patients per group is required. Considering a potential 10% dropout rate, we plan to recruit 64 patients per group, totaling 128 patients.

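### PHN is the primary outcome at 3, 6 and 12 months, but no visit or case rule is named for the single comparison that is planned and sized

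*Protocol article*

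**What the plan says.** Under Outcome Assessment, Primary Outcome, PHN incidence is the "percentage of patients with an NRS score ≥ 4 at the follow-up visits scheduled at 3 months, 6 months, and 12 months". Table 1 marks the row "Incidence rate of PHN" at M3, M6 and M12 alike.

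Under Statistical Analysis, Primary Outcome, the plan is in the singular: "A chi-square test will be used to compare the incidence of PHN between the PRP treatment group and the antiviral therapy group", with one relative risk and its confidence interval. No visit is given. The significance level appears under Secondary Outcomes but is worded for everything: "All statistical analyses will use two-sided tests, with the significance level set to 0.05".

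The Sample Size Calculation uses one pair of rates. The control rate comes from a cited source ("in patients > 50 years of age is approximately 34.8" per cent) and the PRP rate from the team's own experience ("our clinical experience suggests an estimated incidence of 10" per cent). Neither carries a time point. The target is worded "To achieve a 90% confidence level and a 5% significance level", and 58 per group results.

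Study Objectives makes the primary objective the effectiveness of PRP "in alleviating acute ZAP and preventing the onset of PHN". Only the second half has a primary outcome; pain intensity is listed as secondary.

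**The concern.** Three percentages are offered where the analysis and the sample size need one. At least five different primary analyses fit the wording: month 3, month 6, month 12, a case at any visit, or a case at all three. They have different event rates and may lead to different conclusions. Nothing in the protocol stops the choice from being made once results are known, or stops a success at one visit from being reported as success on the primary outcome. Patients and treating doctors know the allocation and the endpoint is the patient's own pain score, so a fixed primary test is one of the main safeguards left.

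The objective adds a second loose end. A favourable result on acute pain could be presented as meeting half of the primary objective, although no primary outcome, power or error rate is assigned to it.

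**Working it through.** **Inputs.** From the Sample Size Calculation: p1 = 0.348, p2 = 0.10, alpha 0.05, 90% (read as power), 58 per group. From the Secondary Outcomes analysis text: two-sided tests. From the primary outcome definition: three visits. The correlation between visits is not in the protocol; 0.5, 0.7 and 0.9 are assumed.

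**1. Reproduce the plan's figure.** The usual pooled formula for a chi-square comparison is

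n = [z(1−α/2)·√(2p̄(1−p̄)) + z(power)·√(p1(1−p1) + p2(1−p2))]² / (p1 − p2)²

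with p̄ = (0.348 + 0.10)/2 = 0.224.

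- √(2 × 0.224 × 0.776) = 0.5896
- √(0.348 × 0.652 + 0.10 × 0.90) = 0.5629
- n = (1.960 × 0.5896 + 1.2816 × 0.5629)² / 0.248² = 57.3, so 58 per group

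This matches the protocol. It shows that the 90% is power and that the trial is sized for exactly one two-sided 0.05 test. Power at 58 per group is 90.4%.

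**2. False-positive rate, if each visit is tested at 0.05 and any success counts.**

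- Independent visits: 1 − 0.95³ = 14.3%.
- Correlated visits: the chance that at least one of three equicorrelated standard normal statistics exceeds 1.96 in absolute value, by simulation with 2 million draws.

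| Assumed correlation of test statistics | At least one false positive |
|---|---|
| 0 | 14.3% |
| 0.5 | 12.5% |
| 0.7 | 10.9% |
| 0.9 | 8.4% |

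A simulation of the binary endpoint itself (58 per arm, correlation 0.5 to 0.9 on the underlying normal scale) gives about 11% to 14%.

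**3. Power, if all three visits stayed primary under Bonferroni.** The per-visit level is 0.05/3 = 0.0167, so z = 2.394. The same rates are assumed at each visit.

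- Power at one given visit, 58 per arm: Φ[(0.248 × √58 − 2.394 × 0.5896)/0.5629] = Φ(0.848) = 80.2%.
- Size for 90% power at each separate visit: (2.394 × 0.5896 + 1.2816 × 0.5629)²/0.248² = 73.97, so 74 per arm.
- Power to succeed at any visit, 58 per arm, by simulation on the normal approximation: about 95%, 92% and 87% for correlations 0.5, 0.7 and 0.9.

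The two kinds of power must be kept apart. The error rates in step 2 count a success at any visit, so the matching power is the 87% to 95%, not the 80%.

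**4. Reading with one case rule.** If a case is pain at any visit, or pain at all three, there is one test, alpha is 0.05 and nothing is inflated. The assumed rates would then have to be rates for that composite, and the protocol does not say that they are.

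**The case against.** The strongest reply is that the protocol speaks of one test and one relative risk, and sizes one comparison, so a single case definition across visits may be intended. That is a fair reading. A reader might infer that the trial definitely takes three chances at 0.05 and so fails to hold its 5% error rate. The text does not support that: the inflation in step 2 follows only if each visit is tested and any success counts.

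A reader might also infer that protecting alpha across three visits must cost the stated 90% power. That does not follow either. Under Bonferroni, power falls to about 80% for a given visit, but power to succeed at any visit is at or above 90% for two of the three assumed correlations. A fixed testing order would leave the first visit at 90%.

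A third tempting reading is that acute pain will be tested at many visits at 0.05 each. The analysis section does list simple two-group tests for NRS-11, but it also provides repeated measures ANOVA or mixed models for repeated continuous data. What stands is only the mismatch between objective and outcome.

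One could add that a statistical analysis plan may settle multiplicity. The method of adjustment can be left there. The identity of the primary endpoint is a protocol matter, and this protocol does not omit it; it states three visits without ranking them. Nor does the Background definition of PHN settle it: pain for at least 3 months after rash healing can be met at any of the three visits.

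**Conclusion.** The point holds as a failure to define the primary endpoint. The protocol names three visits, gives no primary visit and no case rule, and plans and sizes one two-sided 0.05 comparison. The choice of primary test is thus open after the data are seen, and this should be repaired before analysis.

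The size is conditional. With any-visit success at 0.05 each, the false-positive rate is about 8% to 13% for assumed correlations of 0.9 to 0.5, with 14.3% as the figure for independence. With one case rule there is no inflation. The planned 58 per arm is correct arithmetic for a single test; whether it suits the endpoint finally chosen depends on 34.8% and 10% applying to it.

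**What to change.** Name one primary endpoint, tested at two-sided 0.05: either PHN at one visit (for example month 3) or one explicit case rule across the three visits. Make the remaining visits secondary. State the visit or rule in the primary outcome, in the chi-square paragraph and in the sample size paragraph, and replace the word confidence there by power.

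Two checks go with this:

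- The sponsor should confirm that 34.8% and 10% refer to the chosen endpoint. If so, 58 per arm keeps 90% power and the total of 128 need not change. If not, the sample size has to be recalculated.
- The chosen visit should be reconciled with the Background definition of PHN, which counts from rash healing, while the Abstract counts follow-up from the intervention. A month 3 visit need not fall 3 months after healing.

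In Study Objectives, move acute zoster-associated pain to a secondary objective so that the primary objective and the primary outcome agree.

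The cost is wording in the protocol, any analysis plan and the registry entry. The price is that the other visits can no longer carry the primary claim.
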